### Primary and secondary outcomes

The primary outcome is a composite of all-cause mortality and major postoperative complications within 30 days after surgery defined as any of the following: acute myocardial injury (including myocardial infarction), acute kidney injury (all stages), severe infectious complications (including deep surgical site infection, pneumonia, sepsis, peritonitis), anastomotic leakage, pulmonary embolism or venous thrombosis, pulmonary oedema, acute respiratory distress syndrome, *de novo* arrhythmia, stroke, reoperation for any cause, non-fatal cardiac arrest, and mortality.

The outcome is met if any of these events occurred. Definitions of these complications are based on recent guideline papers on standard definitions of outcomes in perioperative medicine.^18^, ^19^, ^20^

Secondary outcomes consist of•Incidence of each of the individual components of the composite primary outcome•Incidence of the composite primary outcome within 7 days after surgery•Incidence of a composite of postoperative infection rate within 30 days of surgery. This is defined as one or more of the following infections: surgical site infection, organ space surgical site infection, urinary tract infection, laboratory-confirmed bloodstream infection or infection, source uncertain (this is defined as an infection which could be more than one of the mentioned infections but it is unclear which)•Clavien–Dindo classification and the modified Comprehensive Complication Index scores based on collected outcomes at postoperative day 30•Hospital length of stay•Incidence of unplanned hospital re-admission within 30 days after surgery•Mortality at 90 days after surgery

An outcome adjudication committee will not be used in this trial. All study outcomes will be prospectively assessed by medical doctors or surgeons or intensive care physicians.

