### Sample size calculation

On the basis of data from previous published studies from our group, the percentage of patients with at least one major postoperative complication using a standard of care practice varies between 45% and 48.7%. As such, we decided to choose 46.5% as the incidence of postoperative complications in the control group. For a classical randomised trial, 466 patients per group (932 patients in total) are needed to show a 20% relative reduction in the primary outcome (from 45% to 36%), using a power of 80% and (two-tailed) alpha risk of 5%. Of note, the main assumption in randomised controlled trials is that the outcome of an individual patient is completely unrelated to that of any other patient (i.e. they are said to be ‘independent’). This assumption is violated in cluster randomised trials as patients within one cluster (centre in our case) are more likely to respond in a similar manner. A measure of this similarity is known as the intraclass correlation coefficient (ICC). Because of this lack of independence, larger sample sizes are required. The ICC values usually described in the literature and reported by the University of Aberdeen on a database dedicated to ICC (https://www.abdn.ac.uk/hsru/what-we-do/tools/index.php) range between 0.005 and 0.05.

The following criteria must consequently be considered when determining sample size for this study: the randomisation sequence (eight periods for each cluster/centre), time periods (3 months), average number of patients per centre (around 15 patients by period), and the coefficient of variation of cluster size, defined as the ratio of the standard deviation (SD) of cluster sizes. To estimate sample size by considering these additional criteria, Stata (StataCorp, College Station, TX, USA) routine stepped-wedge developed by Hemming and Girling has been used. In our trial, 1680 patients (*n*=840 patients by group) are needed to detect a difference between 46.5% and 36% for an ICC value at 0.01, a two-sided type I error at 5%, and a statistical power greater than 80%. To take into account a possible drop-out rate of at least 16% as 30-day follow-up may be difficult in this population, we will include 2000 patients in total. No planned interim analysis will be conducted during the study.

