To compare the incidence of the primary endpoint, a robust random effect Poisson generalised linear mixed model regression with robust variance will be proposed. Intervention groups, steps of randomisation, time periods—treated as categorical variables—and their interactions will be evaluated as fixed effects and centre and time as random effect. Results will be expressed as relative risks and 95% CIs. The estimated intra-cluster correlation and time effect from the fitted model will be reported. Multivariable analysis will use the same statistical model with covariates determined according to unbalanced baseline and to the clinical relevance (type of surgery, ASA score, comorbidities, and AFM compliance). Furthermore, interaction terms in the regression model will be used to test for heterogeneity of effect between subgroups: type of surgery, ASA score, comorbidities, AFM compliance, and anaesthesia duration. Between-group comparisons for other endpoints will be performed using same random effects models taking into account between- and within-centre and time variability (if necessary to obtain a normal distribution, a logarithmic transformation will be considered) or generalised linear. The time-to-event curves will be calculated with the Kaplan–Meier method and compared, when appropriate, using marginal Cox proportional hazards regression model taking into account between-and within-centre and time variabilities (90 days mortality). No missing data are expected for the primary endpoint. For the secondary endpoints, the statistical nature of missing data will be studied, and sensitivity analysis will be proposed to analyse the impact of missing data on results and propose the most appropriate method of imputation. More precisely, missing data mechanisms will be evaluated to determine if data are missing completely at random (MCAR), at random (MAR), or not at random (MNAR). Multiple imputation methods will be considered for handling MAR data, and sensitivity analyses (e.g. complete case analysis, worst-case imputation) will assess the robustness of results.

All analyses will be performed using Stata software (StataCorp). The widths of CIs will not be adjusted for multiplicity and cannot be used in place of hypothesis testing.

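### The reported intra-cluster correlation is taken from a Poisson mixed model fitted to a yes/no outcome, which biases it downward and, at the planned value of 0.01, gives zero in roughly 40–50% of trials

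*Protocol article*

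**What the plan says.** The primary endpoint is a composite scored yes or no for each patient: "The outcome is met if any of these events occurred" (Primary and secondary outcomes).

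For its analysis, "a robust random effect Poisson generalised linear mixed model regression with robust variance will be proposed" (Statistical analysis). Intervention group, randomisation step, categorical period and "their interactions will be evaluated as fixed effects and centre and time as random effect". The same paragraph names two further results: "The estimated intra-cluster correlation and time effect from the fitted model will be reported". It gives no formula or scale for the correlation, and no separate model for it.

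The Sample size calculation section uses an intra-cluster correlation as a design input. It says published values "range between 0.005 and 0.05", and that 1680 evaluable patients are "needed to detect a difference between 46.5% and 36% for an ICC value at 0.01". That is raised to 2000 for a 16% drop-out.

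**The concern.** The article does not leave the source of the reported correlation open: it is the fitted Poisson model. For an outcome with 36% to 46.5% risk, that model credits each centre with more chance variation than a yes/no outcome can have. The data then look under-dispersed to the model, and genuine differences between centres are absorbed into the supposed chance variation. The centre variance shrinks, often to exactly zero. Robust (sandwich) variance is calculated after the fit and does not alter the estimated variance component.

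At stake is a named result of the trial. The reported correlation is how a reader would check the 0.01 on which 1680 and 2000 patients rest. Following the plan exactly could produce a report of no clustering when the planned amount is present.

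**Working it through.** **Inputs from the article.** 16 centres, 8 periods, 7 steps (Trial design, Figure 1 caption); risks 46.5% and 36%, design correlation 0.01, about 15 patients per centre and period, 1680 evaluable and 2000 included (Sample size calculation). Patients per centre: 1680/16 = 105; 15 × 8 = 120; 2000/16 = 125.

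**The plan's own figures.**
- Individually randomised trial, 45% versus 36%: n = [1.960·√(2 × 0.405 × 0.595) + 0.8416·√(0.45 × 0.55 + 0.36 × 0.64)]² / 0.09² = (1.3607 + 0.5818)² / 0.0081 = 465.8, so 466 per group, as in "466 patients per group (932 patients in total) are needed to show a 20% relative reduction".
- Drop-out: 1680/(1 − 0.16) = 2000.
- Stepped wedge: the Hussey–Hughes variance with 1680/128 = 13.1 patients per cell, 46.5% versus 36% and a proportion-scale correlation of 0.01 gives power of 0.84 to 0.85. This agrees with the stated power above 80%, so reading 0.01 as a proportion-scale value fits the plan.

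**Expected loss in the Poisson fit.** Let p = (0.465 + 0.36)/2 = 0.4125, so p(1−p) = 0.2423.
1. Between-centre variance at correlation 0.01: 0.01 × 0.2423 = 0.00242. On the log scale: 0.00242/p² = 0.00242/0.1702 = 0.0142.
2. For a centre with n patients, the Poisson model expects a chance variance of 1/(np) in the log risk. The true value is (1−p)/(np). The excess is p/(np) = 1/n, and it is taken out of the centre variance.
3. Fitted centre variance: 0.0142 − 1/105 = 0.0047; 0.0142 − 1/120 = 0.0059; 0.0142 − 1/125 = 0.0062.
4. As a count-scale correlation (fitted variance × p): 0.0019, 0.0024 and 0.0026. Scale alone accounts for a factor 1/(1−p) = 1.7; the rest is lost variance.
5. Rescaled to proportions (fitted variance × p/(1−p) = × 0.702): 0.0033 at 105 per centre and 0.0044 at 125, against a true 0.01.
6. The expected fitted variance reaches zero when the true correlation is 0.702/n: 0.0067 at 105 per centre and 0.0056 at 125. The planned 0.01 is less than twice that, so zeros will be frequent.

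**Simulation at true correlation 0.01.** Assumptions: centre random intercept; period and intervention fixed effects; cell sizes Poisson-distributed around the mean; maximum likelihood. Zero frequencies come from 2000 data sets per setting, mean Poisson-model correlations from 300, and the linear model from 150.

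| Evaluable N | Poisson centre variance zero | Poisson count-scale mean | Linear model, REML: mean (zero) |
|---|---|---|---|
| 1680 | 48% | 0.0016–0.0019 | 0.0099 (6%) |
| 1920 (15 per cell) | 42% | – | 0.0107 (4%) |
| 2000 | 39% | 0.0020–0.0022 | 0.0099 (3%) |

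Smaller repeat runs gave zeros in 44–52% at 1680, 39–45% at 15 per cell and 38–43% at 2000. A binomial mixed model gave 6–8%. Two other conversions of the same Poisson variance (log-normal formula and binary rescaling) give means of 0.0028 to 0.0042. The understatement is thus about 5- to 6-fold on the count scale and 2.4- to 3.6-fold on the other two.

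**Sensitivity.**
- True correlation 0.005: zero in 68–77%.
- 0.02: zero in 9–16%; count-scale mean 0.007 at N=2000.
- 0.05: zero in under 1% at 15 per cell, but still low (count-scale mean 0.019).
- Step fixed effects added, at 0.01: zero in 80–88% for Poisson, against 8–12% for the REML linear model, whose mean stays at 0.0100–0.0108.

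**Treatment effect.** At 0.01, the effect estimate divided by its standard deviation across data sets is 3.11 for the Poisson model and 3.17 for the binomial model.

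**The case against.** The strongest reply has four parts.

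*The article gives no formula, and the analysis plan may do so.* This stands as a limit on size: no single multiple can be quoted. It does not remove the problem, because the zeros arise in the variance component and no conversion restores them.

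*The simulated model is simpler than the stated one.* Also true. Interactions and a random time effect were not simulated, so no one percentage describes the plan. The one listed addition that was tested, step effects, made matters worse.

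*Zeros belong to the low end of the cited range.* Correct: they are uncommon at 0.02 and rare at 0.05. But 0.01 is the plan's own design value, and the downward bias persists at the higher values.

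*Little depends on the figure.* It feeds no test or decision, and no interim analysis is planned. With 16 centres any estimate is imprecise: at true 0.01 a proportion-scale moment estimator averaged 0.009 with a 95% range of 0 to 0.024. This stands, and it limits the weight of the point. It excuses imprecision, though, not a systematic bias.

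A reader might also infer that the primary comparison or the sample size is undermined. The documents do not support that. Robust variance protects the interval for the relative risk, the two models are almost equally efficient, and the planned power reproduces. Nor can it be shown from the article that later trials would borrow the figure and be undersized.

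**Conclusion.** The point holds for the reported intra-cluster correlation only. Followed as written, the plan derives it from a model whose centre variance is biased downward for a common binary outcome. If the true value is 0.01, the estimate is zero in roughly 40% (N=2000) to 50% (N=1680) of trials, and averages about 2.4 to 6 times too small depending on the unstated conversion. The figure could not be set against the design value in the Sample size calculation section.

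These sizes rest on a centre random intercept, period and intervention effects, maximum likelihood, a mean risk of 0.4125 and assumed variation in cell size, since the article gives no value for the coefficient of variation of cluster size. A zero is not the likelier result in this setting; it becomes so only if the true correlation is nearer 0.005 or the step effects are kept. The primary estimate needs no change. This is a modest but real error in a named result.

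**What to change.** Keep the Poisson model with robust variance for the relative risk. Replace the sentence on the intra-cluster correlation with, for example: *The intra-cluster correlation of the primary outcome will be reported on the proportion scale, with its 95% confidence interval, from a linear mixed model fitted by REML with the same period and intervention terms and a centre random effect; it will not be derived from the Poisson model.*

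Name one estimator. A binomial mixed model would need a further stated conversion to the proportion scale, and in simulation at true 0.01 it averaged 0.0076, about 24% low, where REML averaged 0.0099 to 0.0107.

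The cost is one sentence and one extra model fit on data already held. It needs no patients and does not change the primary estimate. The downsides are that the correlation comes from a different model than the relative risk, and that it stays imprecise with 16 centres, which the confidence interval will show.

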### Randomisation

Randomisation will be performed using block randomisation with a sequence generated in Stata software (version 13; StataCorp) by an independent statistician. The randomisation will be stratified to ensure an alternation of low–medium-volume centres and high-volume centres. The randomisation list will be uploaded into the web-based CleanWeb® (Télémédecine, Boulogne-Billancourt, France) electronic case report form (eCRF) software and forwarded to the sponsor's quality assurance team for validation.

The eCRF (CleanWeb®) also provided clinicians with reminders about the current period (standard of care or AFM). Patients and investigators will not be blinded to treatment allocation. Centres will be notified of their randomisation status only 1 month before transitioning from the standard of care to AFM implementation. This time will be required to upgrade their existing haemodynamic monitoring devices with the AFM software (Edwards Lifesciences).

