### Statistical analysis

Analyses will be performed using Stata software (version 15, StataCorp). Baseline characteristics (centres and patients) will be presented as the mean and standard deviation or the median and interquartile range for each intervention group for continuous data and as the number of patients and associated percentages for categorical parameters. The results will be expressed using standardised differences and 95% confidence intervals (95% CIs). The characteristics of the patients and clusters will be summarised by intervention group to allow consideration for selection biases and lack of balance. Patients will be described and compared between intervention groups at baseline for eligibility and epidemiological, clinical, and treatment characteristics. Protocol deviations and reasons for withdrawal will be described. Other parameters such as the numbers analysed, the average cluster size, cluster characteristics, and important patient characteristics will be compared in each cluster by period. Analysis will be done according to the intention-to-treat principle.

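### Adjustment covariates are picked partly by observed imbalance and include AFM compliance, while the primary model carries no patient-level baseline covariate

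*Protocol article*

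**What the plan says.** All of this is in the protocol article, mostly under Statistical analysis.

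- **Primary model.** "a robust random effect Poisson generalised linear mixed model regression with robust variance will be proposed". Its fixed effects are intervention group, randomisation step, categorical period and interactions: "their interactions will be evaluated as fixed effects and centre and time as random effect". No patient-level covariate is listed.
- **Secondary adjusted model.** "Multivariable analysis will use the same statistical model with covariates determined according to unbalanced baseline". The sentence goes on to a second criterion, so the rule in full is "covariates determined according to unbalanced baseline and to the clinical relevance (type of surgery, ASA score, comorbidities, and AFM compliance". So there are two criteria, imbalance and clinical relevance, and the second names four items. No imbalance threshold is given, nor how the two criteria combine. Comorbidities are not itemised, although the eligibility section lists 14 qualifying conditions.
- **Source of the imbalance judgement.** "Patients will be described and compared between intervention groups at baseline", and characteristics are "summarised by intervention group to allow consideration for selection biases and lack of balance". The same section commits the analysis to intention-to-treat.
- **Recruitment.** Patients give individual written consent and about 40% of those eligible are expected to accept (Recruitment). Patients and investigators are not blinded, and centres learn of their switch one month ahead (Randomisation).

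**The concern.** Three things follow from this wording.

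1. **Imbalance as a selector.** A covariate improves an adjusted estimate because it predicts the outcome, not because the arms happen to differ on it. In a stepped wedge, crude arm comparisons are a particularly poor guide. Control patients come early and intervention patients late, so calendar drift shows up as imbalance even though the period effects already deal with it. The choice is also made after group data have been seen.
2. **AFM compliance as a covariate.** It is observed after allocation and has meaning only under the intervention. Conditioning on it removes part of what the intervention does, so the adjusted estimate no longer answers the intention-to-treat question.
3. **No patient-level covariate in the primary model.** ASA score, surgery type and comorbidities are already regarded as clinically relevant, yet they are kept out of the analysis that decides the trial. That loses precision. It also leaves the primary estimate unprotected if the kind of patient recruited changes when a centre switches.

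**Working it through.** **Reproducing the plan's figures.** For 45% vs 36%, 80% power and two-sided 5%, the standard two-proportion formula gives 466 per group, as stated. Inflating for drop-out, 1680/(1 − 0.16) = 2000, as stated.

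The stepped-wedge figure was checked with the Hussey-Hughes variance. Inputs from Sample size calculation and Figure 1: 8 periods, 7 steps, 15 patients per centre-period, ICC 0.01, 46.5% vs 36%. Assumed layout: two centres per step, since 14 × 8 × 15 = 1680.

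- Mean binomial variance: (0.465 × 0.535 + 0.36 × 0.64)/2 = 0.23959
- Between-centre variance: τ² = 0.01 × 0.23959 = 0.002396
- Cell-mean variance: σ² = 0.99 × 0.23959/15 = 0.015813
- Design constants: I = 14, T = 8, U = 56, W = 560, V = 280
- Var = Iσ²(σ² + Tτ²) / [(IU − W)σ² + (U² + ITU − TW − IV)τ²]
- = 14 × 0.015813 × 0.034980 / (224 × 0.015813 + 1008 × 0.002396) = 0.00130, so SE = 0.0361
- Power = Φ(0.105/0.0361 − 1.96) = 83.0%

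This agrees with the stated power above 80%. With 16 centres and 13.125 patients per cell (also 1680), power is about 84%.

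**Gain from prespecified adjustment.** The documents give no R², so a range is assumed. Only the individual-level variance is multiplied by (1 − R²); the between-centre part stays.

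| Assumed R² | SE (46.5% vs 36%) | Power, 46.5% vs 36% | Power, 46.5% vs 37.2% (20% relative) |
|---|---|---|---|
| 0 | 0.0361 | 83.0% | 72.9% |
| 0.05 | 0.0353 | 84.5% | 74.8% |
| 0.10 | 0.0345 | 86.1% | 76.7% |
| 0.20 | 0.0328 | 89.3% | 80.7% |

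The gain at the design effect is 84.5 − 83.0 = 1.5 points to 86.1 − 83.0 = 3.1 points for R² of 0.05 to 0.10.

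**Does imbalance selection recover that gain?** 2000 stepped-wedge data sets were simulated per scenario, with 14 centres, 8 periods, 15 per cell and six prognostic covariates. The model was linear with fixed centre and period effects. A covariate was selected when its crude arm difference exceeded 1.96 standard errors (an assumed threshold). Fixed centre effects discard between-centre information, so only the contrasts between rows matter, not the absolute power.

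| Analysis | Type I error | Power (20% relative reduction) |
|---|---|---|
| No covariates | 5.0–5.1% | 58% |
| Selected by imbalance | 4.9–5.2% | 59% |
| All six prespecified | 5.0–6.0% | 63–66% |

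The Monte Carlo error on type I error is about √(0.05 × 0.95/2000) = 0.5 points. Reporting the most favourable of these models or any single-covariate model gave 7.8–10.3%.

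**Case-mix exposure.** Assume higher-risk patients have risk 54% and the others 35.25%, and the higher-risk share falls from 60% to 50%, with no treatment effect. The arm risks are 0.6 × 0.54 + 0.4 × 0.3525 = 0.465 and 0.5 × 0.54 + 0.5 × 0.3525 = 0.446, a crude relative risk of 0.960. A Poisson model with centre and period effects (centre fixed, for simplicity) was then fitted to expected values:

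- The shift arises from linear drift common to all centres (3.33 points per period): modelled relative risk 1.000.
- The shift occurs at each centre's own crossover: modelled relative risk 0.960.

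For scale, the design relative risk is 0.36/0.465 = 0.774.

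**The case against.** The best defence has four parts.

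- **The set is partly named already.** Clinical relevance sits in the same sentence and lists surgery type, ASA score and comorbidities. This stands: it would be wrong to say that imbalance alone decides. But imbalance remains a criterion, comorbidities remain open, and AFM compliance is on the named list.
- **The primary result is separate.** A reader might infer that the main result is data-driven or its type I error inflated. The document does not support that. The rule governs only the secondary adjusted analysis, and selection by imbalance did not by itself raise type I error in simulation. Inflation appeared only when the most favourable of several models was reported, which the protocol does not propose.
- **Period and centre effects protect the primary estimate.** This stands for drift common to all centres. A reader might take the 0.96 as a bias that the primary model always keeps; it survives only if case mix changes at each centre's own switch. The Blinding section argues that selection bias is unlikely because operations cannot be predicted. With individual consent, unblinded investigators and a month's notice of the switch, such a change is possible, but nothing in the document shows that it occurs.
- **Detailed covariate lists belong in the SAP.** This is true of detail, but the selection rule is stated here, and an SAP that follows it inherits both faults.

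A reader might also object that centre volume, used to order the randomisation ("The randomisation will be stratified to ensure an alternation of low–medium-volume centres and high-volume centres"), is missing from the model. That is minor: volume is a centre-level attribute, and the model already has a centre random effect and step terms.

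**Conclusion.** The point holds as a weakness in prespecification and efficiency, not as an error in the primary test. Imbalance should not select covariates. AFM compliance does not belong in an adjustment set under intention-to-treat; this is the clearest fault and needs no assumption.

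The precision forgone is modest: about 1.5 to 3 power points for R² of 0.05 to 0.10 at 46.5% vs 36%, and about 2 to 4 points at 46.5% vs 37.2%. These sizes rest on the assumed R², the 14-centre layout and a variance formula simpler than the planned model. The primary test is valid if recruitment is unbiased. The remaining exposure is to case-mix change at crossover. Its illustrated size, a relative risk of 0.96, depends wholly on the assumed risks and shift.

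**What to change.** Before data are seen:

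1. Name a fixed set of baseline covariates: type of surgery, ASA score, age and an itemised list of comorbidities.
2. Include that set in the primary model, and report the model without patient-level covariates (group, step, period and centre terms only) as a sensitivity analysis.
3. Delete baseline imbalance as a selection criterion. The descriptive baseline summary can stay.
4. Remove AFM compliance from the adjustment set.

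The cost is SAP wording and a few more model parameters. Comorbidities are recorded at inclusion (Table 1), and surgery type and ASA score are already planned covariates, so little or no new data collection should be needed. The sample size need not change, because the stated 1680 does not rely on adjustment.
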